### Study design

A quasi-experimental pre-post design will consist of an intervention group of participants undergoing the JMoF program and a control group comprising of participants from the program waitlist who are waiting for at least 10 weeks until program entry. Recruitment to each group will be based on program start date and will not be subject to randomisation. Randomisation was not possible as it would not allow participants any choice as to when and with whom they participated in the program – which are important aspects of the JMoF program design [20].

Intervention participants will be surveyed at three time-points: program commencement, program completion (10 weeks) and at six months post program completion. Controls drawn from the waitlist will be surveyed at two time-points: 10 weeks prior to program commencement and on completion of their 10 weeks on the waitlist (which will correspond to their program entry). A time-three measurement will not be obtained from controls as it was considered neither feasible nor acceptable for the waitlist controls to have to wait a further six months before entering the program (equivalent to the intervention follow-up period); this potentially would lead to a high drop-out rate both from the evaluation and the program itself. However, for one of the primary outcome measures, vegetable intake, Queensland state-wide monitoring data will be used as a proxy time-three measure for the control group.

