### The Jamie Oliver Ministry of Food program, Australia

This methods paper describes the evaluation framework and design for the Jamie Oliver Ministry of Food program (JMoF) Australia, Ipswich site. The JMoF program was originally developed by Jamie Oliver, a renowned celebrity chef and food author based in the United Kingdom (UK). JMoF Australia has been specifically adapted for the Australian setting. It is a community focused program that teaches basic cooking skills and good nutrition to non-cooks. It consists of 10, weekly, 1.5 hour cooking skills classes aimed at getting people of all ages and backgrounds cooking simple, fresh, healthy food quickly and easily [11]. Participants pay AUD10 per class and, where this may pose a barrier to entry, subsidies are made available.

JMoF was pioneered as a community-based cooking skills program in Rotherham, UK in 2008 and since then, other centres have opened in Bradford and Leeds and a mobile centre in the North West of the UK. These centres were reliant on funding mostly from local councils and to a lesser extent, charities and the private sector. The first Australian site opened in Ipswich in the state of Queensland in April 2011 co-funded by a local philanthropic non-government organisation (NGO), The Good Foundation (TGF), and the Queensland Department of Health. Ipswich was intentionally chosen given its significant low socio-economic status population [12] and increasing levels of overweight and obesity [13].

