### Recruitment

All participants registered on the JMoF Australia waitlist database, aged 18 years or over, and who had received a confirmed start date for the program, will be eligible to participate in the quantitative component of the evaluation. Whilst the program is open to all members of the Ipswich community over the age of 12 years, the evaluation will target the adult population only as other cooking skills programs exist within the Greater Ipswich region that are specifically targeting children and adolescents in educational settings.

All participants will be required to consent prior to participation in the evaluation. A link to the questionnaire will be embedded within an email generated by the JMoF program database, inviting program participants to participate in the evaluation questionnaire.

Recruitment to both groups will be based on confirmed program start dates. As control participants are required to be on the program waitlist for 10 weeks and because the JMoF waitlist is sufficiently large to enable this to occur naturally, participants that are allocated a start date longer than 10 weeks ahead, will be automatically made a control, whilst persons commencing the program within 10 weeks will be assigned to the intervention group. Computer programmed “rules” in the JMoF participant database have been created to automate this process.

To show appreciation for participation, those intervention participants who complete the third and final questionnaire at six months post completion of the program will be sent a $20 “Good Guys” store charge card redeemable at any Good Guys store (white goods retailer) across Australia.

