### Data analysis

Demographic and baseline characteristics will be summarised for both intervention and control groups using standard summary statistics (mean and standard deviation) and non-parametric statistics (medians and inter-quartile ranges) where applicable. Frequencies and percentages will be reported for categorical variables. The magnitude of change both within and between intervention and control groups for T1, T2 and T3 time-points will be assessed. For continuous data, such as fruit and vegetable intake, two sample t tests will be employed to compare means between intervention and control groups at each time point and paired t tests for within group comparisons. A split-plot in time Anova will be used as the basis for these t-tests. For categorical data, frequencies will be reported for intervention and control groups and chi squared analysis will provide between group comparison results. Regression analysis will be conducted to determine the potential contribution of specific demographic factors on the outcome variables of interest. All data analysis will be performed using STATA S.E. 12.0 statistical software.

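### The six-month vegetable comparison sets program enrollees against a state-wide sample, so it mixes any program effect with an unestimated enrollee–population difference; cooking confidence has no six-month comparator

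*Protocol article*

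**What the plan says.** The Study design section sets the follow-up. Intervention participants are surveyed at "program commencement, program completion (10 weeks) and at six months post program completion". For the comparison group, "Controls drawn from the waitlist will be surveyed at two time-points", ten weeks apart, and "A time-three measurement will not be obtained from controls" because a further six-month wait was judged neither feasible nor acceptable. For vegetable intake only, the section then fills the gap: "Queensland state-wide monitoring data will be used as a proxy time-three measure for the control group".

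The Data analysis section makes no exception for T3: "The magnitude of change both within and between intervention and control groups for T1, T2 and T3 time-points will be assessed". It names two-sample t tests between the groups at every time point for continuous outcomes and paired t tests within groups, all resting on a split-plot ANOVA.

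Two other statements show who is being compared. Under Recruitment, those eligible are "All participants registered on the JMoF Australia waitlist database, aged 18 years or over, and who had received a confirmed start date for the program". In the background section on the program in Australia, "Ipswich was intentionally chosen given its significant low socio-economic status population"; the same section describes the program as aimed at people who do not cook. On allocation, Study design says: "Recruitment to each group will be based on program start date and will not be subject to randomisation".

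**The concern.** At T1 and T2 the comparison is between two sets of people who signed up for the same program and differ in start date. At T3 the control becomes a different population: state survey respondents, who need not have sought a cooking class and need not live in a low socio-economic area. A difference in usual vegetable intake between these populations would enter the T3 contrast in full, and a larger sample would not reduce it.

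At stake is the only measurement after the program ends, on a primary outcome. A pre-existing difference in one direction could be taken for a lasting benefit; in the other direction it could hide one. For cooking confidence the between-group T3 comparison, read literally, cannot be carried out, because no comparator exists.

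**Working it through.** **1. The plan's own figure.** The Sample size section gives 250 per group for 0.5 serves/day, from a baseline mean of 2.5, at 80% power and 0.05 significance. It states no SD, so the figure cannot be reproduced. By the two-sample normal approximation (two-sided) it implies an effective SD of 0.5 × √(250/2) / (1.960 + 0.842) = 5.590 / 2.802 = 1.995 serves/day. The calculation assumed an interaction test, so this need not be the cross-sectional SD. A range of 1.0 to 2.0 is therefore assumed below.

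**2. What the T3 contrast estimates.** Let μ_I, μ_W and μ_P be the mean intakes, without the program, of intervention enrollees, waitlist enrollees and the state population. Let τ be the program effect at T3 and s a calendar trend common to all.

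- Level contrast at T3: (μ_I + τ + s) − (μ_P + s) = τ + (μ_I − μ_P).
- Change from T1, using waitlist controls at T1 and the state at T3: [(μ_I + τ + s) − μ_I] − [(μ_P + s) − μ_W] = τ + (μ_W − μ_P).

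Both contain an enrollee-minus-population term. Taking change from baseline does not cancel it, because the control series switches population between T2 and T3.

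**3. Whether the stated plan removes the term.** The Survey instrument section aligns the vegetable question with the state survey. That addresses how intake is asked, not who is asked. The regression on demographic factors in Data analysis is not described as adjusting the proxy comparison. No restriction, matching or weighting of the state data is stated. The Discussion acknowledges sampling and participation bias and relies on the waitlist control for attribution; it does not mention the proxy.

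**4. Illustrative size.** Assumptions: τ = 0 at T3, 250 intervention responders, two-sided 0.05, offset b in serves/day. Two cases bound the precision of the state figure:

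- state mean treated as known: SE = SD/√250, which is 0.0632 at SD 1.0 and 0.1265 at SD 2.0;
- state sample of only 250: SE = SD × √(2/250), which is 0.0894 at SD 1.0 and 0.1789 at SD 2.0.

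The probability of a significant result is 1 − Φ(1.96 − b/SE) + Φ(−1.96 − b/SE). For b = 0.25 and SD 2.0, b/SE is 1.976 with a known mean and 1.398 with 250 respondents, giving 0.507 and 0.287. At SD 1.0 the ratios are 3.953 and 2.795, giving 0.977 and 0.798.

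| Offset b | SD 1.0: 250 proxy respondents to known mean | SD 2.0: 250 proxy respondents to known mean |
|---|---|---|
| 0.1 | 20% to 35% | 9% to 12% |
| 0.25 | 80% to 98% | 29% to 51% |
| 0.5 | about 100% | 80% to 98% |

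An offset of 0.25 is half the effect the study is sized for (0.25/0.5). An offset of −0.25 would bring the expected contrast for a true effect of 0.25 to zero.

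**5. Cooking confidence.** Study design limits the proxy to vegetable intake and obtains no T3 data from controls, whereas Data analysis promises between-group change at T3 without limiting it by outcome. The two passages do not fit together for this outcome.

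**The case against.** The strongest defence is that the protocol calls the state data a proxy and does not say how it will be used: as a level, as a change between survey rounds, or as context. A condensed article may leave that to a fuller plan. The split-plot interaction test in the Sample size section is tied to the waitlist design, which most naturally means T1–T2, and the T3 wording in Data analysis can be read as applying where data exist. Because the question is aligned and both groups are measured at T1, the baseline enrollee–state gap could be described from data already planned. That gap may be small: the assumed baseline of 2.5 serves/day comes partly from the population survey itself. Finally, the illustration assumes full retention; with 150 responders at SD 2.0 and a known state mean, SE = 2.0/√150 = 0.163, and an offset of 0.25 gives about 33% rather than 51%.

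Much of this stands as a limit on the size of the concern: the document establishes neither a non-zero gap nor its direction. It does not remove the concern. The text makes the state data the control group's T3 measure, plans between-group tests at each time point, and commits to no check or correction of the offset.

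A reader might infer more than the documents support:

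- That the T3 contrast measures only who enrols. It contains any program effect as well; the two cannot be separated.
- That the state sample excludes Ipswich. It is only not restricted to Ipswich.
- That state records will be entered into the paired tests or the ANOVA, or that the T3 result will be tabulated beside the T2 result as a sustained effect. The document does not say so.

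**Conclusion.** The point holds in limited form. As written, the T3 between-group comparison of vegetable intake cannot isolate a sustained program effect, because it carries an enrollee–population difference that the stated plan does not estimate. For cooking confidence there is no T3 comparison to make. The T1–T2 contrast with the real waitlist is not affected by this point, nor is the within-intervention change to T3, which is uncontrolled.

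The structural conclusion needs no numerical assumption. The size does: the 29% to 98% range for a 0.25 serves/day offset rests on an assumed offset, an assumed SD of 1.0 to 2.0, 250 T3 responders and no program effect. The document fixes none of these for T3. It should be corrected before analysis because it concerns a primary outcome at the only follow-up after the program.

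**What to change.** - **Study design:** stop using state-wide data as a proxy T3 control.
- **Data analysis:** limit between-group inference to T1–T2 for both primary outcomes. Report T3 as within-intervention change (T1–T3 and T2–T3) with confidence intervals, labelled uncontrolled and without a between-group p-value.
- **State data, if shown:** present only the change in the state mean between survey rounds, as descriptive context for secular trend, alongside the baseline enrollee–state gap. Differencing the state's own series removes a fixed offset, but not differences in motivation to change or regression to the mean, so it should stay descriptive.
- **Interpretation:** state that no controlled six-month effect is claimed.

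This changes wording only and needs no new data collection from participants. The cost is a weaker six-month claim.

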### Survey instrument

In collaboration with key stakeholders, a quantitative measurement tool was developed. The self- administered questionnaire was designed to be completed in approximately 15 minutes. Given the lack of validated and reliable survey tools which can accurately measure the impacts and outcomes of cooking skills programs in varying population groups [21], a prototype questionnaire was designed to address the unique objectives of the evaluation. Where suitable, specific questions were incorporated that have been previously used to measure the impact of cooking skills programs, particularly on cooking confidence and cooking behaviours such as those used by Barton et al, 2011 [21].

To measure the primary outcome of cooking confidence as a proxy for cooking self-efficacy, questions were developed addressing confidence in relation to specific cooking skills based on Short’s work [22] and Barton et al. 2011 work [21]. These items are presented on a 5 point Likert confidence scale ranging from ‘not at all confident’ to ‘extremely confident’.

The other primary outcome measure of change in vegetable intake will be captured through self-report questions of vegetable intake (serves per day) and aligned with baseline measurement questions of the same nature used by Queensland Health in its population-based self-reported health surveys [23]. Survey items addressing specific secondary outcome measures such as self- reported mean daily fruit intake and mean daily takeaway/fast food intake were also aligned with corresponding questions from the same baseline population health survey [23].

Other secondary outcome items include measuring change in the self-reported frequency of cooking the main meal from basic ingredients and the inclusion of salad or vegetables with the main meal. Nutrition knowledge questions, aligned with the nutrition messages embedded within the program, will test knowledge around salt, fat and sugar intake and have been adapted from Parmenter et al’s work [24].

Participant attitudes towards cooking and eating healthy foods, willingness to try new foods, enjoyment and satisfaction in cooking and eating healthy foods will be tested, using Likert scale based questions. Questions about shared enjoyment of cooking, eating and normative eating behaviours were adapted from questions from The Stephanie Alexander Kitchen Garden Evaluation (SAKG) [25]. The Rosenberg Self-Esteem Scale (RES), a widely validated and reliable measure of self-esteem, will also be administered [26]

Participants will be asked to report their total household food and drink (excluding alcohol) expenditure and expenditure specifically on take-away food and fruit and vegetables. Height and weight will be self-reported to enable the calculation of Body Mass Index (BMI).

### Piloting

The questionnaire was piloted in a 3 step process to test the design, content and potential delivery methods. Following comment by the reference group and academic colleagues on content and layout/design, a paper-based version of the questionnaire was piloted with a sample (N = 30) of the current JMoF population. Feedback was invited through informal focus group sessions, facilitating the identification of any questions that were ambiguous, sensitive or required further development.

The final stage of piloting involved testing the questionnaire in an online format whilst simultaneously testing the online survey distribution system and the likely response rate. As the survey distribution required integration between the JMoF participant database and the survey platform, Qualtrics™ [27], the piloting tested that these two components were effectively integrated and capable of providing the necessary information needs.

### Recruitment

All participants registered on the JMoF Australia waitlist database, aged 18 years or over, and who had received a confirmed start date for the program, will be eligible to participate in the quantitative component of the evaluation. Whilst the program is open to all members of the Ipswich community over the age of 12 years, the evaluation will target the adult population only as other cooking skills programs exist within the Greater Ipswich region that are specifically targeting children and adolescents in educational settings.

All participants will be required to consent prior to participation in the evaluation. A link to the questionnaire will be embedded within an email generated by the JMoF program database, inviting program participants to participate in the evaluation questionnaire.

Recruitment to both groups will be based on confirmed program start dates. As control participants are required to be on the program waitlist for 10 weeks and because the JMoF waitlist is sufficiently large to enable this to occur naturally, participants that are allocated a start date longer than 10 weeks ahead, will be automatically made a control, whilst persons commencing the program within 10 weeks will be assigned to the intervention group. Computer programmed “rules” in the JMoF participant database have been created to automate this process.

To show appreciation for participation, those intervention participants who complete the third and final questionnaire at six months post completion of the program will be sent a $20 “Good Guys” store charge card redeemable at any Good Guys store (white goods retailer) across Australia.

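### The start-date rule does not guarantee that the two groups' 10-week windows share calendar weeks, and the stated comparison has no calendar term, so seasonal change in diet can enter the program effect

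*Protocol article*

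**What the plan says.** Under Study design, the protocol article states that "Recruitment to each group will be based on program start date and will not be subject to randomisation". The Recruitment section gives the rule, automated in the program database: "participants that are allocated a start date longer than 10 weeks ahead, will be automatically made a control", while "persons commencing the program within 10 weeks will be assigned to the intervention group". It explains that the 10-week control wait is workable "because the JMoF waitlist is sufficiently large to enable this to occur naturally".

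The survey times differ by group. Intervention participants are surveyed at "program commencement, program completion (10 weeks) and at six months post program completion". Controls are surveyed "10 weeks prior to program commencement and on completion of their 10 weeks on the waitlist". The control window is therefore the 10 weeks before program entry, and the intervention window is the 10 weeks after it.

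In the Data analysis section, "two sample t tests will be employed to compare means between intervention and control groups at each time point", on the basis of a split-plot ANOVA. The regression that follows concerns demographic factors. The section mentions neither calendar time nor season, and the article states no requirement that the groups accrue in step.

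**The concern.** A wait-list control is there to remove change that would have happened without the program. It does this only if both groups are followed over comparable weeks. The Discussion relies on it: the wait-list control and the pre and post measures are said to support attributing change to the program. The same section acknowledges sampling and selection bias, but not bias from calendar period.

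Vegetable intake is a primary outcome, and fruit and takeaway intake are secondary. All three could plausibly vary over the year. If one group's windows sit mostly in one season and the other's in another, the difference in change contains a seasonal part. Demographic adjustment would not remove it, because it belongs to the survey dates and not to the people. The argument is made for dietary intake only; nothing here shows the same mechanism for cooking confidence, the other primary outcome.

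**Working it through.** The plan gives no figure for seasonal change, so there is none to reproduce. The check asks when the windows coincide and how large the bias could be if they do not.

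**Inputs.** From the article: the 10-week cut-off (Recruitment), the windows before and after entry (Study design), and the target of 0.5 serves a day (Sample size). Assumed: a 52-week sinusoidal season with amplitude A of 0.1 to 0.2 serves a day (0.2 to 0.4 peak to trough), at the phase that gives the largest bias.

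**Step 1: alignment.** An intervention participant starting in week S has the window S to S + 10. A control starting in week C has the window C − 10 to C. The windows are identical when C = S + 10. At any moment, people due to start in 0 to 10 weeks are intervention and those due in 10 to 20 weeks are controls, so a steady flow with that spread gives matching windows.

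**Step 2: bias for one pair of windows d weeks apart.** The largest difference in 10-week seasonal change is 4 × A × sin(10π/52) × sin(πd/52), where sin(10π/52) = 0.568.

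| d (weeks) | A = 0.1 | A = 0.2 |
|---|---|---|
| 0 | 0 | 0 |
| 5 | 0.07 | 0.14 |
| 10 | 0.13 | 0.26 |
| 13 | 0.16 | 0.32 |
| 26 | 0.23 | 0.45 |

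For example, at A = 0.2 and d = 13: 4 × 0.2 × 0.568 × 0.707 = 0.32. These are values for a single pair. Group means average over many weeks and generally give less.

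**Step 3: the rule applied to simulated entry.** People enter evenly over the accrual period with gap g. If g is 10 or less, they are intervention and the window starts at entry + g. Otherwise they are controls and the window starts at entry + g − 10. The bias is proportional to A, so the values below halve at A = 0.1.

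| Pattern of gaps (A = 0.2) | Accrual | Worst-phase bias (serves/day) |
|---|---|---|
| Steady, spread over 0–20 weeks | 26 or 52 weeks | about 0 |
| Steady, spread over 0–30 weeks | 26 weeks | 0.08 |
| Steady, spread over 0–30 weeks | 52 weeks | about 0 |
| Mean falls 14 to 8 weeks; SD 2, 4, 6 | 52 weeks | 0.16, 0.09, 0.06 |
| Mean falls 16 to 6 weeks; SD 2, 4, 6 | 52 weeks | 0.24, 0.15, 0.10 |
| 75% controls in first half, 25% in second | 26 or 52 weeks | 0.13 |
| Only controls in first half, only intervention in second | 26 or 52 weeks | 0.27 |

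Across a wider set of drift paths, spreads and accrual lengths, the range at A = 0.2 was 0.01 to 0.32. The low end came from long accrual, where each group's windows cover most of the year.

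**Step 4: effect of the remedy.** With calendar month of the T1 survey as a fixed effect in the analysis of change, the remaining bias was 0.03 serves or less in every drift scenario.

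**The case against.** The strongest reply is that the rule has alignment built in. Because controls are measured before entry and intervention participants after it, a control starting 10 weeks later than an intervention participant has exactly the same window. Step 1 confirms this, and steady recruitment gives a bias of about 0. This stands, and it limits the point.

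A reader might infer something stronger: that the rule itself fills the groups in different periods, with every new registrant becoming a control while the waitlist is long. The article does not say so. It says the list is long enough for a 10-week wait to arise naturally, and the same sentence provides for people who start sooner. Eligibility turns on a confirmed start date, not on registration, and participants choose when they attend, so gaps would vary among people entering in the same week. Scenarios that give everyone in a given week one identical wait force all-control or all-intervention weeks. A constant 12-week wait over 70 weeks would make only about 12% of entrants intervention, which does not fit 250 per group.

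The benign case is also an assumption, however. The article does not say that gaps will stay spread around 10 weeks during accrual.

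It can also be said that a calendar covariate is ordinary analysis-plan detail, and no such plan is shown. That is fair against any claim that no adjustment exists anywhere. The point is narrower: the article fixes an assignment rule and a form of comparison, neither of which secures concurrent windows. Adjustment in a later plan works only where windows overlap, which recruitment has to secure.

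**Conclusion.** The point holds as a conditional risk. Concurrent windows are possible under the rule but not assured, and the stated comparison would not correct a mismatch. At an assumed amplitude of 0.1 to 0.2 serves a day, the worst-phase bias runs from near 0 to about 0.3 serves, so at its upper end it could exceed half of the 0.5-serve target (0.3/0.5 = 60%). Where in that range the trial falls depends on how far waits drift, how widely they are spread and how long accrual lasts, none of which the article states. The bias can have either sign. The size of the seasonal swing and its phase are assumptions, so the documents do not support saying that seasonal change does enter the effect, or by how much.

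**What to change.** 1. Include calendar month, or intake block, of the T1 survey as a fixed effect in the between-group analysis of change. The date follows from start dates already in the program database.
2. Monitor accrual by group and calendar block so that windows overlap. The existing database rules can be used to keep controls who start about 10 weeks after an intervention block as that block's concurrent comparison.
3. Report the 10-week windows of each group by calendar period, so that readers can judge the overlap.

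The cost is a few degrees of freedom, and less precision where overlap is thin. If the groups separated completely in time, the calendar term would be nearly collinear with group and could not rescue the comparison, which is why step 2 is needed.

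Comparing intervention T1 with control T2, both taken at program entry, should not be offered as a test of period effects alone. It mixes period with the effect of waiting and of answering the survey a second time.
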